## Abstract

**Background:**

Caries risk assessment is an essential element for managing and preventing dental caries in children. Individual caries risk assessment can be conducted to evaluate the presence or absence of single factors, or using multivariate models, a combination of factors. The subject has been extensively studied, but no previous research has compared whether a more elaborate and individualized method of caries risk benefits the patient than more straightforward strategies. Thus, this protocol evaluates the efficacy of two risk assessment methods for caries control in children, a simplified method based on caries experience evaluation and a multivariate method described in the literature.

**Methods:**

This is a randomized, double-blind, controlled, parallel-treatment trial protocol. Two groups will be tested for two forms of caries risk assessment: an individualized and detailed multivariate method based on the guidelines of the Caries Care International 4D and another simplified process, based only on caries experience in primary and/or permanent dentition, considering the presence of decayed, missing and filled teeth using the DMFT/dmft index. Participants will be children aged 8 to 11 years, followed up at 12 and 24 months. The primary outcome will be a composite outcome representing the number of tooth surfaces requiring operative intervention (account variable). In addition, the Shapiro–Wilk normality test and Student's t-test will be performed. A multivariate analysis using negative binomial regression will compare groups in the intention-to-treat population, considering a two-tailed significance level of 5%.

**Discussion:**

This is the first randomized clinical trial aiming to compare dental caries-related treatment and follow-up based on a detailed, multivariate and individualized assessment of caries risk in school-age children to a simpler risk assessment strategy based on caries experience. This study will define whether there are essential benefits to the patient that justify the choice of one method over the other.

*Trial registration* Clinicaltrials.gov registration: NCT03969628. Registered on May 31th, 2019.

**Supplementary Information:**

The online version contains supplementary material available at 10.1186/s12903-021-02010-3.

## Introduction

Dental caries is considered a multifactorial dynamic disease, determined by the interaction of biological, behavioral, and psychosocial factors related to the individual's environment [1]. There has been a continuous decline in the caries prevalence and lesions progression in the last decades [2]. However, unequal distribution of the disease burden in the population is still observed, and poorer children with low access to dental services are more affected [3].

Authors have stated that caries risk assessment can prevent the onset of the disease or its evolution and, thus, could contribute to guide public interventions and allocate time and resources to those most needed [4]. In addition to being considered an essential element for management and prevention of dental caries, caries risk assessment, could establish the appropriate follow-up appointments [5–7].

The main goals of caries risk assessment are determining the patient's probability of developing new caries lesions in a given period and the risk of present lesions progressing to more severe stages [5, 6]. There are mainly two ways to assess individual caries risk: (a) simple assessment based on factor’s presence or absence, and (b) assessment by multivariate models, a combination of more than one variable, classifying the patient’s caries risk [6, 8].

Several studies about caries risk assessment with children and adolescents were carried out and are summarized in systematic reviews [8–11]. Most primary studies have cohort design and were conducted to determine isolated variables that would have adequate predictive power for developing new carious lesions [12]. Those were unanimous in stating that the past caries experience is the factor with the strongest association with an increased risk of dental caries. In the cohort study by Hall-Scullin, et al., they show that children who had caries lesions in the primary dentition and those who were caries-free at this stage had very different trajectories in the development of new caries lesions in the permanent dentition; hence the authors suggest different prevention strategies for these two groups of children [12].

However, other authors claim that past caries experience would not be the ideal prediction method, especially in the new era in which dentistry is of minimal intervention and non-operative approaches concerning the management of dental caries [5]. Multivariate methods have been proposed to improve this prediction power [5, 6, 8, 11, 13]. Some authors claim that multivariate models have better predictive power than individual clinical indicators, especially preschool children [6, 7]. However, to date, there is no scientific evidence that supports choosing one factor or method over another, and none are very accurate in predicting the development of new lesions. At most, they can be considered having moderate evidence level [10, 14].

Although authors and clinical protocol guides have emphasized the importance of individualized caries risk assessment for the correct management and non-operative treatment of patients [4, 7, 13, 15], this assumption is mainly based on expert’s opinion. Furthermore, the studies on which the guides are based are of low methodological quality [14], and are focused on identifying the factors or models that predict new injuries.

No study has been carried out to assess whether a more elaborate and individualized method of caries risk assessment, considering a combination of several factors, provides more effective prevention and treatment related to dental caries. Moreover, there is no information regarding potential benefit to the patient, compared to more straightforward strategies, as caries experience in primary and/or permanent dentition. This would ideally be answered through a randomized clinical trial comparing the two strategies.

Thus, a randomized clinical trial will be conducted to evaluate two methods of assessing children’s caries risk. This protocol will compare dental caries-related treatment and follow-up based on a detailed, multivariate and individualized assessment of caries risk in children to a more uncomplicated risk assessment strategy based on caries experience.

## Methods

### Trial design

This is a randomized, double-blind, controlled, parallel trial-treatment trial. Two groups will be tested regarding caries risk assessment: individualized and detailed method, considering several risk predictors, based on the guidelines of the Caries Care International 4D [4, 5, 16], and another simplified method, based only on the caries experience in deciduous and/or permanent dentition, considering the index of decayed, missing and filled teeth (DMFT/dmft) [12]. The groups will receive treatment and follow-up procedures based on their form of caries risk assessment.

The study was registered in the ClinicalTrials.gov clinical database (Identifier: NCT03969628), approved by the Research Ethics Committee from the School of Dentistry, Federal University of Pelotas (UFPel) (#3.282.962) and reported following the guidelines of the “Standard Protocol Items: Recommendations for Interventional Trials” (SPIRIT), detailed in the Additional file 1.

### Participants, intervention, and outcomes

#### Setting

The study will be conducted at the Pediatric Dentistry Clinical of Dental School, Federal University of Pelotas (UFPel). Children from 8 to 11 years old who seek assistance at the location will be eligible, after duly authorized by the guardians, through free informed consent and the child's consent.

#### Eligibility: inclusion and exclusion criteria

The study will include children who meet the following criteria: (1) 8 to 11 years old, (2) who were referred or seeking dental treatment at the college and have been screened by the Pediatric Dentistry Clinical, (3) residents in the city from Pelotas/RS or nearby region (not exceeding 50 km of distance). In addition, children will be excluded: (1) wearing fixed appliances, (2) with systemic problems or with any disability that lead to difficulty in understanding the guidelines and the questionnaire, (3) with a history of absences (up to 2 attempts to schedule an interview and exam), (4) with an expected change of city and region (cities 50 km far from Pelotas), (5) manifesting behavioral problems already in the screening clinical appointment, specifically, that present the classification “generalized protest” or “more intense protest” according to the Brazilian Version of the VENHAM Scale (BvVBRS). They will be referred to behavior management consultation [17].

#### Intervention

Two ways of assessing the risk of dental caries will be tested so that this study will have two intervention arms:

Multivariate Group: Children classified as low and high risk for caries and treated based on the Caries Care International 4D manual [15, 16], in which different caries risk profiles are directed to different strategies for caries management.

Simplified Group: Children classified as low and high risk for caries based only on past and current caries experience in primary and/or permanent dentition and treated according to that [12].

The Caries Care International 4D are a series of clinical protocols for diagnosis and treatment decisions related to non-operative and operative procedures aimed to maintaining health and preserving tooth structure [16]. One of the key elements is the individual assessment of the patients' caries risk, which leads to a treatment based on prevention, control, and minimally invasive surgical treatment personalized according to the needs of each patient, as well as a follow-up with intervals based on the initial risk [4, 15]. The individualized and detailed method is based on several risk predictors, and its latest update proposes the classification of the patient as low and high risk [16] (Fig. 1).

**Fig. 1 Fig1:**
[figure not shown]
Classification of caries risk according to the criteria

The risk assessment based only on caries experience in primary and/or permanent dentition, considering decayed, missing, or filled teeth by caries, according to the criteria of the World Health Organization (WHO) [16], will be the criterion choice of the simplified group. Thus, children will be classified as low, with no past or current caries experience (DMFT/dmft = 0) and high risk, with history or current caries experience in primary and/or permanent dentition (DMFT/dmft > 0) and will be treated and followed-up based on clinical caries exam [12] (Fig. 1).

The risk assessment criteria are shown in Fig. 2. For the Multivariate group, a practical method of association of caries risk factors and protective factors will be used, represented by colors: red and black for risk factors, green for the protective factors. The patient will be evaluated according to their presence or absence, resulting in a final sum that will classify the child as high or low risk. For example, a patient with any risk factor (red color) is considered high risk. Those with risk factors (black color) receive 1 positive point for each factor present. Those with caries protective factors receive 1 negative point. If the patient does not have risk factors in red, which already puts him at high risk regardless of the score, the risk of final caries will be given through a combination based on a summation of risk factors (+) (black color) and protective (−) (green color). Having a combination of factors with a final sum ≥ 3 classifies the patient as high risk. Patients classified as low risk are those with a final sum ≤ 2 [16].

**Fig. 2 Fig2:**
[figure not shown]
Simplified and multivariate caries risk assessment criteria

#### Interview, examination procedures, and treatment of participants

The child legal guardian will answer a semi-structured questionnaire regarding data needed for the risk assessment criteria listed in Fig. 2. Demographic and socioeconomic data will be collected, such as: sex, age, income, parents' education, and skin color. In addition to the standard questions aimed at providing comprehensive care to the child, the caregiver will be asked about the diet to identify sugar consumption and oral hygiene (regularity and use of fluoride toothpaste). This interview will address specific questions included in the risk assessment (criteria 8–16) (Fig. 2).

The clinical examination will follow a sequence, initially the absence or presence of: thick dental plaque, areas of plaque stagnation (high biofilm retention), and erupting molars will be evaluated. Afterward, a trained and calibrated evaluator will assess the condition for dental caries according to the WHO criteria through the DMFT/dmft index (decayed, missing, and filled teeth) [16]. Then, a professional toothbrushing will be carried out with fluoride toothpaste, and the same trained and calibrated evaluator will assess caries using the International Caries Detection and Assessment System (ICDAS) index in its simplified form [16]. Caries activity will be analyzed using the visual criteria proposed by the NYVAD System and finally the complementary PUFA/pufa index (pulp involvement, ulceration due to root fragments, fistula and abscess for permanent and primary teeth) [16].

After the interview and clinical examination, the researcher will conduct the caries risk assessment expressed in Fig. 1, using the criteria proposed by Caries Care International 4D [15, 16], together with caries experience in primary and/or permanent dentition. The mother's caries experience will be evaluated using the DMFT index only if the score referring to the mother's exam can change the classification; this will be the last item to be listed [16]. The participant will be classified using both methods: simplified and multivariate, by the same researcher. Only after complete classification they will be randomized into one of the groups and follow the intervention and subsequent clinical procedures according to their group, shown in Fig. 3.

**Fig. 3 Fig3:**
[figure not shown]
Caries risk guide and clinical management

The multivariate group follows the protocols proposed by the Caries Care International 4D that guide prevention strategies and early management of dental caries. General advice on diet and oral hygiene are common for high and low-risk patients (brushing twice a day with fluoride toothpaste above 1000 ppm of fluoride). Patients classified at high risk are recommended to be approached with motivational interview techniques for behavior modification, prescription of mouthwash as one of the home care and clinical approaches including: fluoride applications (varnish or gel) after dental prophylaxis if the child has active carious lesions (two to four applications weekly) and sealant on all permanent molars. The scheduled return intervals for low-risk patients are six to eight months and high-risk patients three to four months. In these high-risk patients, the application of fluor gel or varnish is recommended at each visit.

For the simplified group, care protocols that are a consensus in clinical practice were used, following the current routine in the unit (Dental School—UFPel). Both patients classified as high and low risk received general advice on diet and oral hygiene (brushing twice a day with fluoride toothpaste above 1000 ppm fluoride). Among the interventions and clinical approaches unique to high-risk patients in the simplified group are: sealing permanent molars on surfaces classified as at risk after evaluation, for example, molars with deep grooves and retention factors. And the fluoride applications (varnish or gel) after dental prophylaxis if the child has active caries lesions (two to four applications with a weekly interval). The maintenance of the return visits has the interval: patients classified as low risk nine to twelve months, high-risk patients five to six months the returns.

### Randomization, implementation, and blinding

The randomization strategy used will be in permuted blocks with sizes of 4, 6 and 8 and stratified by age (8 to 9 years; 10 to 11 years) and the child's caries experience (DMFS/dmfs ≤ 4; DMFS/dmfs > 4). First, all participants will be evaluated for caries risk by the two strategies, and then participant randomization will be performed in the same session. The allocation sequence used will be obtained from the website www.sealedenvelope.com, and sealed in sequentially numbered opaque envelopes by a researcher without any contact with the practical research procedures.

Another researcher will be responsible for including the participants. Although the groups to which children will be allocated will not be revealed to children and their parents, due to differences in treatments and mainly different intervals for return visits in the two groups, it is difficult to maintain blinding throughout the study for all participants. Therefore, the outcome assessors at 12 and 24 months will be blinded to groups. The groups will be coded in the data analysis worksheets for blinding those who will carry out the statistical analysis. Breaking blinding will not be allowed under any circumstances for outcome evaluators.

### Follow-up visits

Participants will return at intervals determined by the patient's individual risk, according to groups. These appointments were considered as part of the allocated intervention and will follow clinical management protocols according to your group. After 12 and 24 months they will also return to collect the outcomes. A new risk assessment will be performed, following the protocol to which the child was initially allocated, as well as a further clinical examination that will reassess: plaque dental caries, condition, and activity through the DMFT/dmft, ICDAS, NYVAD, and PUFA complementary index [18, 19]. The researcher responsible for the inclusion will carry out this reassessment, and if necessary, a new treatment plan will be developed. Two trained and calibrated examiners, blind in relation to the groups to which the participants were allocated and without participation in the dental treatments, will re-examine the children. After the re-examination, the child will follow the standard re-evaluation procedure described above and will be referred for treatment, if necessary.

### Outcomes

The primary outcome will be a composite outcome representing the number of tooth surfaces requiring operative intervention in two years of follow-up. Thus, the primary outcome will be the sum of surfaces with new carious lesions involving dentin, restored surfaces that needed replacement, and those teeth needing endodontic treatment or extraction (accounting for 4 or 5 surfaces per tooth, for anterior or posterior teeth, respectively). If the tooth surface requires two types of treatment at different times, the treatment will be computed twice.

Secondary outcomes will be the components of the primary outcome considered separately: surfaces with new lesions involving dentin, restored surfaces in need of restoration replacement, teeth with episodes of pain, need of endodontic treatment and extraction. Besides that, costs accumulated for 24 months, health-related quality of life (HRQOL), and oral health-related quality of life (OHRQOL) will also be collected as secondary outcomes.

In order to assess the cost of going to the appointments during the 2 years of follow-up questions about travel will be collected: “What transport do you normally use to come to the appointments?”; “How many buses do you take to come?—If the person uses a bus.”; and “How long does it take, approximately, from leaving home until arriving at the dental school?”.

The HRQOL will be collected using the Brazilian version of the KIDSCREEN-52 [20] and for OHRQOL the Brazilian version of the Child Perceptions Questionnaire (CPQ) [21] will be used. The questionnaires will be applied by trained interviewers before the clinical examination.

For the economic evaluation, a specific analysis plan of economic economic will be prepared. The main economic hypothesis will be if using the multivariate (more complex) assessment may be an efficient manner of allocating resources. A societal perspective and a 24-month time horizon were adopted. Resources spent during the trial follow-up will be registered and then, appropriately valued as costs. The effects to be tested will be derived from the assessed outcomes: number of new operative interventions alongside 24 months, changes in DMFT after 24 months and Quality of life. Then, cost-effectiveness analyses will be performed.

### Timeline

The participant will be followed for 24 months, at 12 and 24 months, return consultations will be held for risk assessment and outcome collection. The other appointments will be according to caries risk assessment. The study phases are described in Fig. 4.

**Fig. 4 Fig4:**
[figure not shown]
Standard protocol items timeline, enrolment, registration, feedback, and evaluations

### Sample size

The sample estimation was based on the primary outcome, which is the number of tooth surfaces in need of surgery during follow-up. Therefore, the following possibilities were considered to compose this outcome:New caries lesions;Restorations in need of replacement;Dental extractions (5 surfaces per tooth);Resolution of pain episodes and/or need for endodontic treatment (5 surfaces per tooth).

To perform the sample calculation, incidence data were collected for all possibilities in the literature, reaching an average occurrence of 17.6 new decayed surfaces in 2 years [22], 10% failure of occlusal-proximal and composite resin and glass ionomer occlusal restorations, which gives an average of 0.1 surface with the need to change for occlusal restorations and 0.2 surfaces in 2 years [23], 0.08 tooth extractions for caries in two years, totaling 0.2 surfaces [24] and 0.2 pain episodes in 2 years on average, leading to an average of 1 surface treated in 2 years. Thus, the estimate of surfaces in need of surgical treatment in 2 years is an average of 19. It was considered that the reduction of 5 surfaces in need of treatment would be a significant number. The expected mean for the test group would be 14. The expected standard deviation values for the control and test groups are 15 and 10, respectively [22–24]. Considering a significance level of 0.05 and a power of 0.80, using a two-tailed test, the minimum number of children per group calculated was 103. Considering a sample loss of 20%, the final rounded number required of 250 children was reached.

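### The 20% loss allowance multiplies by 1.2 instead of dividing by 0.8, so 250 children leave 100 per group against a stated minimum of 103 (t-test power about 79%); separately, the extraction component should be 0.4 surfaces, not 0.2

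*Protocol article*

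**What the plan says.** All the figures are in the Sample size section of the protocol article.

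- **Control mean.** It is built from literature components. New decay comes first ("reaching an average occurrence of 17.6 new decayed surfaces in 2 years"). Restoration failure follows, entered as 0.1 and 0.2 surfaces, then extractions ("0.08 tooth extractions for caries in two years, totaling 0.2 surfaces"), then 0.2 pain episodes counted as 1 surface. The total is rounded: "the estimate of surfaces in need of surgical treatment in 2 years is an average of 19". The list of components in the same section gives an extracted tooth 5 surfaces.
- **Target difference.** It is set directly: "It was considered that the reduction of 5 surfaces in need of treatment would be a significant number". The test-group mean is therefore 14. The standard deviations are 15 (control) and 10 (test).
- **Size before loss.** "Considering a significance level of 0.05 and a power of 0.80", and "using a two-tailed test, the minimum number of children per group calculated was 103".
- **Size after loss.** "Considering a sample loss of 20%, the final rounded number required of 250 children was reached".

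**The concern.** The section calls 103 per group a minimum and 250 the number required once 20% loss is allowed for. Those two statements should agree: 250 children less 20% should leave at least 206. They leave 200. If the loss is as large as planned for, the trial ends below its own minimum and the stated 80% power is not quite reached.

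The extraction figure does not follow from the weight given a few lines above it. It feeds the expected control mean, so one has to check whether correcting it disturbs the calculation.

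**Working it through.** **Inputs, all from the Sample size section:** difference 5; SDs 15 and 10; two-sided alpha 0.05; power 0.80; loss 20%; total 250. Two assumptions: allocation is 1:1 (one number is given per group, and no other ratio is stated), and loss is equal in the two arms.

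**1. Size before loss (the plan's own figure).**
n per group = (1.960 + 0.8416)² × (15² + 10²) / 5² = 7.849 × 325 / 25 = 102.04, rounded up to 103. The noncentral-t power at 103 per group is 80.0%. The stated 103 reproduces.

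**2. Loss allowance.**
- As apparently done: 206 × 1.2 = 247.2, rounded to 250. This matches the stated total.
- As needed: 206 / (1 − 0.20) = 257.5, so 258 (129 per group). The stated total is 8 children lower.

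**3. What 250 delivers.**
- At 20% loss: 250 × 0.80 = 200, or 100 per group.
- Loss that still leaves 206: 1 − 206/250 = 17.6%. That this percentage matches the 17.6 decayed surfaces is coincidence.

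**4. Power at 100 per group.**
Standard error = √(325/100) = 1.803, and 5 / 1.803 = 2.77.

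| n per group | Normal approximation | t-test | Welch |
|---|---|---|---|
| 103 | 80.4% | 80.0% | 79.9% |
| 100 | 79.2% | 78.8% | 78.8% |

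On the t-test the shortfall is 80.0 − 78.8 = 1.2 percentage points.

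**5. Extraction component.**
- Stated: 0.08 teeth counted as 0.2 surfaces.
- At the stated weight: 0.08 × 5 = 0.4. At the 4 surfaces that the Outcomes section allows for anterior teeth it is 0.08 × 4 = 0.32, so neither weight gives 0.2.
- The pain component is scaled correctly (0.2 × 5 = 1), so this looks like a slip and not a different convention.
- Sum as stated: 17.6 + 0.1 + 0.2 + 0.2 + 1 = 19.1. Sum corrected: 17.6 + 0.1 + 0.2 + 0.4 + 1 = 19.3. Both round to 19.
- The formula in step 1 uses only the difference and the SDs, which the plan sets directly. With those unchanged, n stays at 103.

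**The case against.** The strongest reply is that nothing of substance is lost. The shortfall is about one percentage point, less than the uncertainty in SDs taken from the literature. The Data analysis section also plans a negative binomial regression, and on the plan's own means and SDs that comparison does better. The implied dispersions are (225 − 19)/19² = 0.571 and (100 − 14)/14² = 0.439. The variance of the log rate ratio at 100 per group is (1/19 + 0.571 + 1/14 + 0.439)/100 = 0.0113, and the power is about 82%. All of this stands, and it is why the point is minor. It does not make the sentence right: the 80% and the 103 belong to a comparison of means, and for that comparison 250 with 20% loss does not give what is stated.

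A reader might go further in three ways that the document does not support.

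- **That the component slip causes the loss of power.** It does not. The difference and SDs are fixed separately, and the shortfall comes from the loss step alone.
- **That the restoration component is also mis-scaled.** Entering a 10% failure proportion as 0.1 and 0.2 surfaces fits one restoration of each type per child. The document gives no number of restorations per child, so no error can be shown.
- **That 17.6 new decayed surfaces conflicts with the randomisation strata**, which split baseline DMFS/dmfs at 4, so that a 5-surface reduction might be out of reach. The trial is "stratified by age (8 to 9 years; 10 to 11 years) and the child's caries experience", but a cut-point is not an expected mean, and the upper stratum has no ceiling. The Discussion describes a sample with high caries experience. The document gives no basis for a much lower control mean, so power figures that assume one are not findings about this plan.

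**Conclusion.** Two arithmetic slips in the Sample size section are certain, and both are minor.

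1. The loss allowance was applied by multiplication. At the planned 20% loss, 250 children leave 100 per group, below the stated minimum of 103, and t-test power is about 79% (78.8%) instead of 80%. This rests on the plan's own difference and SDs, 1:1 allocation and equal loss in the arms.
2. The extraction component is 0.4 surfaces, not 0.2. The control mean still rounds to 19, and neither the sample size nor the power changes.

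This is an inaccurate statement of what 250 delivers, not a material failure of the design.

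**What to change.** Keep 250 and correct the wording of the Sample size section.

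- Restate the final sentence in one of two ways: with 20% loss, 250 children leave 100 per group and about 79% power for the t-test; or 250 children allow for 17.6% loss while keeping 103 per group.
- Change the extraction component from 0.2 to 0.4 surfaces and the underlying sum to 19.3. The rounded mean of 19, the difference of 5 and the 103 per group stay as they are.

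The cost is two edited sentences and a stated power about one point lower. No extra children, visits or procedures are needed. The article reports the study as suspended and possibly resuming, so the wording can be put right before then.
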